# Efficacy and safety of self-administered acupressure on symptoms, quality of life and nasal mucosal function in patients with perennial allergic rhinitis: study protocol for a randomized controlled exploratory trial

**DOI:** 10.1186/s12906-023-04132-3

**Published:** 2023-08-30

**Keywords:** Allergic rhinitis, Acupressure, Specific acupoints, Self-administered, Randomized controlled trial

## Abstract

**Introduction:**

Allergic rhinitis is a global health problem that can potentially be managed through acupressure. Our clinical observations have identified Allergic Rhinitis Acupressure Therapeutic (ARAT) as a novel acupressure treatment acting on specific acupoints, which may enhance the effectiveness of acupressure. Therefore, we propose a three-arm randomized controlled trial will be conducted to investigate the efficacy and safety of ARAT for perennial allergic rhinitis (PAR).

**Methods/design:**

In this trial, eligible 111 participants diagnosed with PAR will be randomly assigned to one of three groups: the ARAT group, the non-specific acupoints group, or the blank control group. The primary outcome will be the change in the total nasal symptom score, and the secondary outcomes will include: 1) changes in the scores of the standard version of Rhinoconjunctivitis Quality of Life Questionnaire (RQLQs); 2) acoustic rhinometry and anterior rhinomanometry; 3) changes in the scores of relief medication usage; 4) incidence of adverse events. Additionally, we will measure and compare the changes in cytokine levels (IL-5, IL-13, IFN-γ, and TSLP) in nasal secretions.

The RQLQs and primary outcomes will be assessed at the beginning, middle, and end stages of the treatment period, with monthly follow-ups conducted over a total of three months. The secondary outcomes and biomarkers in nasal secretions will be measured at the beginning and end of the treatment period. Any adverse events or need for rescue medication will be carefully noted and recorded.

**Discussion:**

This study may produce a new acupressure treatment prescription that is easy to learn, more targeted, and adaptable. This trial represents the first clinical investigation comparing ARAT treatment for PAR with the non-specific acupoints group and blank control group. Our data is expected to provide evidence demonstrating the safety and efficacy of ARAT for PAR patients, while also exploring the functional mechanism underlying ARAT treatment, moreover, the results offer valuable insights for healthcare professionals in managing PAR symptoms.

**Trial registration:**

Chinese Clinical Trial Registry, ChiCTR2300072292. Registered on June 08, 2023.

**Supplementary Information:**

The online version contains supplementary material available at 10.1186/s12906-023-04132-3.

## Background

Allergic rhinitis (AR) is a prevalent global health issue associated with a rising prevalence, imposing a substantial medical and economic burden. It is attributed to the immunoglobulin E (IgE)-mediated immune response of the nasal mucosa and involves various immune cells such as type 2 innate lymphocytes (ILC2s), T helper 2 (Th2) cells, follicular helper T cells, B cells, dendritic cells, and epithelial cells in its pathogenesis [1, 2]. AR is characterized by symptoms including sneezing, itching, running nose, and nasal obstruction [3], which can be classified as perennial or seasonal based on their correlation with specific pollen or mold spore exposures [3]. The prevalence of AR varies among different geographic regions, affecting 10%–40% of adults worldwide [4, 5]. Notably, the prevalence of AR has shown a progressive increase from 19% in 1990 to 32% in 2017 among Danish individuals aged 18-69 years [6], and in China, the standardized prevalence of adult AR has increased by 6.5% from 2005 to 2011 [7]. Epidemiological studies have revealed that approximately 16% of Americans are affected by AR [8].

While AR is not life-threatening, poorly controlled AR can lead to compounded effects and various comorbidities such as asthma, allergic conjunctivitis, chronic rhinosinusitis, and upper airway cough syndrome [3, 9]. Current therapeutic methods for AR management include patient education, allergen avoidance, pharmacotherapy, allergen-specific immunotherapy [1, 8], and surgical treatment [3, 4]. Although these approaches can effectively control most AR symptoms, they often present limitations such as incomplete relief, slow onset, less than 24-hour relief, and reduced efficacy with sustained use [10]. Additionally, poor adherence to pharmacotherapy is observed in a significant number of patients [1]. Approximately 20% of patients experience inadequate control of AR symptoms and continue to suffer from disruptive or troublesome symptoms [11–13]. Consequently, patients are increasingly drawn to complementary and alternative medicine as a potential solution [14]. utilizing these therapies to improve the management of perennial allergic rhinitis (PAR). In addition to adhering to standardized treatment guidelines for AR, we believe that the development of a complementary and alternative treatment approach that is easy-to-learn, self-implement, and effectiveness for patients is essential. Therefore, the efficacy and safety of acupressure will be evaluated in this trial.

Acupressure, also known as acupoint massage therapy, involves applying pressure to specific points on the body using fingertips. It is a well-established complementary and alternative therapy with a long history of use in use in treating various diseases in China. As a subtype and noninvasive alternative to acupuncture, which has been demonstrated to be effective and safe for PAR [8], acupressure is easy to administer and has been widely used for clinical treatment in mainland China, Taiwan, Hong Kong, South Korea, Germany, and Australia [15–19]. Two meta-analyses [16, 17] have indicated that acupressure for AR is both safe and effective. Previous studies have shown that acupressure is effective, safe, and well-tolerated in alleviating AR symptoms [18, 19]. Our research team has identified a specific combination of acupoints for AR, which is simple to apply and easy to learn. This treatment approach has been named Allergic Rhinitis Acupressure Therapeutic (ARAT) to facilitate recognition and recall.

Given the considerable therapeutic potential of acupressure as a daily treatment practice and with the aim of improving PAR management in daily life, we hypothesize that self-administered ARAT will provide a therapeutic, safe, and cost-effective option for patients with PAR. However, robust scientific evidence is needed to guide the clinical application of acupressure. Therefore, this trial seeks to investigate the efficacy and safety of ARAT in alleviating PAR symptoms, improving quality of life in adults with PAR, and exploring the feasibility of telehealth for PAR management. Two control groups, the non-specific acupoints group and the blank control group, will be included for comparison purposes.

## Methods

### Design

This study has been designed as a prospective, three-arm, randomized, controlled trial (RCT) and will be conducted at the Second Clinical College of Guangzhou University of Chinese Medicine (SCCGZUCM), also known as Guangdong Provincial Hospital of Chinese Medicine, in Guangzhou, China. The planned start date for this clinical trial is July 2023, and it is estimated to end by April 2024. The flowchart of the trial is provided in Fig. 1 and Table 1. The trial will consist of a 2-week run-in period, a 4-week intervention period, and a 12-week follow-up period. The study protocol has been developed in accordance with the Standard Protocol Items: Recommendations for Interventional Trials (SPIRIT) guidelines (Additional File 1) [20]. To ensure accurate interpretation and easy replication, the acupressure protocol will adhere to the Revised Standards for Reporting Interventions in Clinical Trials of Acupuncture (STRICTA), which is a formal extension of the Consolidated Standards of Reporting Trials (CONSORT) Statement [21]. Additionally, the intervention will be reported following the guide and model for Intervention Description and Replication (TIDieR) [22].

**Fig. 1 Fig1:**
[figure not shown]
Flow chart of the clinical trial procedures. ARAT, Allergic Rhinitis Acupressure Therapeutic; TNSS, total nasal symptom score; RQLQs - Rhinoconjunctivitis Quality of Life Questionnaire score; AcRh, AcRhacoustic rhinometry; AnRh, AnRhanterior rhinomanometry

**Table 1 Tab1:**
[figure not shown]
Schedule of trial enrolment, intervention, assessment and follow-up

*ARAT* Allergic Rhinitis Acupressure Therapeutic, *TNSS* Total nasal symptom score, *RQLQs* Rhinoconjunctivitis Quality of Life Questionnaire score

### Participants

Patient candidates were recruited through local media and doctor referrals. Interested candidates underwent a phone interview with our research assistants. Prior to their first visit, the study information and consent forms were sent to the participants for them to review. They were informed that nasal secretion samples would be collected. Screening evaluations were conducted and recorded during the first visit to ensure the eligibility of each participant who was willing and met the trial’s criteria. Subsequently, the research assistants obtained signed consent forms.

### Eligibility

#### Inclusion criteria

Participants must have a diagnosis of PAR according to the diagnostic criteria [3, 8, 9]; Participants must be aged between 18 and to 65; There are no gender restrictions; Participants must have the ability to communicate orally; Participants must be capable of completing the case report forms (CRF) independently or with the assistance of the investigator when necessary; Participants must volunteer to participate in the trial and provide informed consent.

#### Exclusion criteria

Participants with acute rhinitis, vasomotor rhinitis, and other non-allergic chronic rhinitis; Participants with localized skin lesions, such as burns, eczema, ulcers, or chilblains; Participants who are pre pregnant or menstruating (after menstruation, treatment can be initiated, and the date should be noted); Participants with dyssomnia or behavioral disorders that would hinder unable their cooperation with the study; Participants who are prone to being lost to follow-up; Participants using systemic or local hormones for asthma or other diseases.

#### Elimination criteria

Participants who have been enrolled in the study but cannot receive the assigned treatment at any stage due to various reasons; Participants who experience severe adverse events requiring their withdrawal from the study; Participants who do not fully participate in treatment or follow-up; Participants who do not meet the inclusion criteria but have been accidentally included; Participant who fail to comply with the treatment or provide important information for evaluation.

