### Safety assessment

Participants will be asked to report any AEs, which are defined as any undesirable experiences [36]. They will have access to the research team members at any time. The occurrence time, severity, management, and causality of AEs will be recorded on CRFs. All AEs will be followed up until resolved, and severe AEs will be reported to the Ethics Committee of SCCGZUCM within 24 hours. Monitoring AEs in this trial serves the purpose of ensuring participant safety and dealing with adverse events in a timely manner, in addition to being a secondary outcome measure.

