### Quality control and data management

To ensure adherence to the study protocol and familiarity with the administration process, all members involved in this program, including therapists, operational assistants, nurses, and statisticians, underwent systematic training before the trial commenced. The therapists responsible for applying the treatment possess Chinese medicine licenses, and both the therapists and nurses are familiar with the location of acupoints. All relevant information is recorded in CRFs, and the TNSS and RQLQs scales are carefully collected. Data entry follows the double-entry method using EpiData 3.1 software, and regular checks are performed to maintain data quality, with modifications recorded by a research assistant. Another research assistant conducts a double check of the data for any discrepancies and promptly notifies the manager if any are found. These two assistants are independent from the sponsor and have no competing interests with the authors. After repeated audits and logical checks to ensure the accuracy of the database, two sets of data will be locked and backed up for analysis. If participants withdraw from the trial at any stage, their reasons will be recorded, and the dropout rate will be analyzed statistically.

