### Statistical analysis

Qualified statisticians who are blinded to the treatment group data will perform all efficacy and safety analyses following the intention-to-treat (ITT) principle using SPSS 20.0 (IBM SPSS Inc., Armonk, New York, USA). Missing values will be estimated using the last recorded data. A significance level of α= 0.05 will be considered statistically significant. The median, minimum, and maximum values will be used to express measured data. Group comparisons will be analyzed using Analysis of Variance (ANOVA) and pairwise comparisons (rank-sum test for univariate variance). Count data will be expressed as composition ratios or rates, and comparisons between groups will use the χ2 test for efficiency and rank-sum test for efficiency and rank-sum test for ranked data.

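### The elimination criteria do not say what elimination does; read as removal from the analysis, they conflict with the intention-to-treat commitment

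*Protocol article*

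**What the plan says.** The Eligibility section of the protocol article has three lists: inclusion, exclusion and elimination. The third concerns people already in the trial. Apart from those enrolled in error, its grounds are:

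- Allocated intervention not received, whatever the cause: "Participants who have been enrolled in the study but cannot receive the assigned treatment at any stage due to various reasons"
- Harm that ends participation: "Participants who experience severe adverse events requiring their withdrawal from the study"
- An incomplete course or incomplete visits: "Participants who do not fully participate in treatment or follow-up"
- Poor adherence or missing data: "Participant who fail to comply with the treatment or provide important information for evaluation"

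The list states no consequence. It does not mention an analysis set, removal of data or replacement of participants.

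The Statistical analysis section says that the statisticians "will perform all efficacy and safety analyses following the intention-to-treat (ITT) principle", and that "Missing values will be estimated using the last recorded data". For participants who withdraw, Quality control and data management says that "their reasons will be recorded, and the dropout rate will be analyzed statistically". Safety assessment describes adverse-event monitoring as a means of protecting participants, "in addition to being a secondary outcome measure".

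**The concern.** Intention to treat keeps exactly the people on the elimination list: those who never received, stopped or only partly followed their allocated intervention, and those who left because of harm. If the list governs who is analysed, the primary comparison is not an intention-to-treat comparison, whatever its label.

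Three features of this trial make that matter:

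- **Knowledge of the arm.** The Blinding section says that investigators and participants know the allocation. The statisticians are to be blinded, but that does not protect a decision made before the data reach them. The article gives no threshold for full participation. It describes both nightly practice and 20 sessions in 4 weeks, which has 28 nights; those two statements need reconciling, and until then it is unclear what a complete course is.
- **Unequal exposure.** Only the two acupressure arms have sessions, app check-ins and weekly technique calls to miss.
- **Safety.** Adverse-event incidence is a secondary outcome, and one elimination ground is a severe adverse event that leads to withdrawal.

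**Working it through.** **1. The two possible readings**

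| Reading of elimination | Fit with Statistical analysis | Consequence |
|---|---|---|
| Removal from the analysis | Conflicts with intention to treat for efficacy and safety, and leaves last-value imputation little to do, since people with incomplete follow-up are gone | Exclusions after randomisation that may be related to outcome |
| End of study participation, data kept | Compatible | TNSS after elimination may go uncollected and be filled with the last value |

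The first reading is the natural one. Withholding evaluation information and having been enrolled in error are reasons to set data aside, not reasons to stop acupressure. The severe-adverse-event ground covers people who are already withdrawing. No sentence in the article rules either reading out.

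**2. Which comparisons are exposed**

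- *ARAT versus blank control:* the ARAT arm has sessions and check-ins; the blank arm keeps its usual routine. Both have the mometasone spray, the relief-medication diary and the TNSS and RQLQs assessments through follow-up week 12. The difference in exposure is the acupressure requirement only.
- *ARAT versus non-specific acupoints:* the control arm follows the same procedure, so the burden is equal and any bias may largely cancel.

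**3. The plan's own figure**

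From 33 per group and 10% dropout: 33 / 0.9 = 36.7, rounded up to 37; 37 × 3 = 111. This reproduces the stated total. If eliminated participants are left out, 37 × 0.9 = 33.3, 37 × 0.8 = 29.6 and 37 × 0.7 = 25.9 remain per arm at 10, 20 and 30% elimination. The inflation covers only the first.

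**4. Illustration of the shift**

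Let p be the share of one arm that is eliminated and g the shortfall in improvement of the eliminated relative to the retained. The mean of the whole arm is (1 − p) × retained mean + p × eliminated mean, so the retained mean overstates it by p × g.

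Neither p nor g is in the article. Assume p = 0.10 to 0.20, g = 1 to 2 TNSS points, and elimination in one arm only. For the type I error assume also no true effect and SD = √((1.7² + 1.6²)/2) = 1.65, from the pilot post-intervention SDs of the ARAT and blank arms. The standard error is 1.65 × √(1/37 + 1/(37(1 − p))), and the error is the two-sided normal approximation at nominal 0.05.

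| p | g | Shift p × g | Type I error |
|---|---|---|---|
| 0.10 | 1 | 0.1 | 0.057 |
| 0.10 | 2 | 0.2 | 0.080 |
| 0.20 | 1 | 0.2 | 0.078 |
| 0.20 | 2 | 0.4 | 0.166 |

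For scale, the pilot ARAT-versus-blank difference is 7.3 − 5.1 = 2.2 points after the intervention. In change from baseline, the form in which the abstract states the primary outcome, it is (9.7 − 5.1) − (10.1 − 7.3) = 4.6 − 2.8 = 1.8 points. A shift of 0.4 is 18% of the first and 22% of the second.

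**The case against.** The best defence is that the article has only one statement on who is analysed, the intention-to-treat sentence, and that the elimination list sits under Eligibility and says nothing about analysis. Last-value imputation makes sense only if people with incomplete data stay in, and withdrawal is described as something to be recorded and counted. Analysis sets may be defined in a fuller protocol or analysis plan that is not shown.

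Much of this stands. The absence of a per-protocol definition is not itself a fault, and the article does not prove that anyone will be removed. What remains is that the list has no stated purpose and its natural sense contradicts the analysis section.

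A reader might infer three stronger things that the documents do not support:

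- **That severe adverse events will be dropped from the safety results.** The ground is limited to events requiring withdrawal. The outcome and safety sections require adverse events to be recorded and followed until resolved, and severe ones to be reported to the ethics committee. Loss from the incidence analysis is possible, not stated.
- **That the blank arm can hardly be eliminated.** Its medication, diary and follow-up requirements can also trigger the list.
- **That the bias must favour ARAT.** That is plausible against blank if those who miss sessions improve less. But an open blank arm could lose more people to follow-up, so the net direction is not known.

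**Conclusion.** The point holds as a conflict conditional on the natural reading. Elimination is undefined; if it means removal from the analysis, it cannot stand beside intention to treat for all efficacy and safety analyses. The risk of bias falls mainly on ARAT versus blank, and a risk of losing participants withdrawn for severe adverse events from the incidence analysis goes with it.

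The article supports no estimate of size. The 0.1 to 0.4 point shift, and the type I error of about 0.06 to 0.17, rest wholly on assumed elimination rates, assumed shortfalls and elimination in one arm. The 10% in the sample-size section is a dropout allowance, not an elimination rate. The conflict should be settled before the data are examined, so that the analysis population is not chosen with results in view.

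**What to change.** Reconcile Elimination criteria and Statistical analysis by stating that:

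1. participants who meet an elimination criterion stay in the intention-to-treat efficacy analysis, in the arm to which they were randomised, and in the safety analysis with all their adverse events;
2. their TNSS and RQLQs visits continue where they agree;
3. any exclusion from the primary analysis is limited to ineligibility shown by data from before randomisation;
4. the elimination list defines only a secondary per-protocol analysis, labelled as such.

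This concerns who is followed and analysed. It sets no rule on when treatment stops. The planned 111 does not change. The cost is protocol wording and a few more follow-up contacts.

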### Sample size

The primary outcome measure is Total Nasal Symptom Score (TNSS). As there are no existing studies on ARAT, a new type of acupressure, the sample size calculation was based on a pilot study of ARAT for PAR that utilized the same outcome measure (Table 2). Using these results and considering the study's objectives, the sample sizes for the ARAT group and the non-specific acupoints group were separately calculated for comparison with the blank control group. The calculations were performed with α=0.05 and β=0.1, and the maximum sample size for each group was determined to be 33 cases using PASS11.0 (NCSS, LLC. Kaysville, UT, USA) software. Accounting for a potential 10% dropout rate, a total sample size of 111 participants will be recruited for this trial, with 37 participants allocated to each group.

**Table 2 Tab2:** Pilot study of ARAT for perennial allergic rhinitis

	**the ARAT group**	**the non-specific acupoints group**	**the blank control group**

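### 33 per group is not the larger of the two pilot-based calculations described: non-specific acupoints versus blank control has about 7% power at that size on post-intervention TNSS, not 90%

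*Protocol article*

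**What the plan says.** The Sample size section of the protocol article takes its inputs from the pilot results in Table 2. It states that "the sample sizes for the ARAT group and the non-specific acupoints group were separately calculated for comparison with the blank control group". The error rates are given as follows: "The calculations were performed with α=0.05 and β=0.1". The larger of the two results is then adopted: "the maximum sample size for each group was determined to be 33 cases". "Accounting for a potential 10% dropout rate", the total becomes 111, "with 37 participants allocated to each group".

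The section names TNSS as the measure but does not say whether the post-intervention score or the change was used, and it gives no sidedness and no SD. The abstract says: "The primary outcome will be the change in the total nasal symptom score". Table 2 prints means and SDs before and after the intervention for each arm. It gives no SD of change and no pre-post correlation.

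**The concern.** The paragraph gives the data source, the two contrasts, the error rates, the rule (take the maximum) and the result, so it can be checked. After the intervention, the non-specific and blank arms of the pilot differ by only 0.2 TNSS points, with SDs of 1.6 to 1.9. A calculation at 90% power on so small a difference cannot give a few dozen per group, and a maximum over two calculations cannot lie below either of them.

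What is at stake is how one contrast will be read. The Discussion says the effect of pressing the non-specific points needs to be determined in this trial, and the Statistical analysis section plans pairwise comparisons. A reader told that non-specific versus blank was sized at β = 0.1 could take a non-significant result as evidence that these points do nothing. At the pilot effect the trial could not show that.

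**Working it through.** **Inputs (Table 2, TNSS, mean ± SD)**

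| Arm | Pre | Post | Improvement |
|---|---|---|---|
| ARAT | 9.7 ± 2.2 | 5.1 ± 1.7 | 4.6 |
| Non-specific | 9.5 ± 2.0 | 7.1 ± 1.9 | 2.4 |
| Blank | 10.1 ± 1.7 | 7.3 ± 1.6 | 2.8 |

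α = 0.05, taken as two-sided because sidedness is not stated; power 0.90; equal allocation. The pre-post correlation r is not reported, so a range is assumed.

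**Formulas.** Pooled SD = √[(SD₁² + SD₂²)/2]. By the normal approximation, n per group = 2(1.960 + 1.2816)² × (SD/Δ)² = 21.01 × (SD/Δ)². The results below use the exact two-sample t calculation, which adds about one per group. For change, each arm's SD = √(SDpre² + SDpost² − 2r·SDpre·SDpost).

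**Step 1: the plan's own figures.** The dropout step reproduces: 33/0.9 = 36.7, rounded up to 37, and 3 × 37 = 111. The 33 does not reproduce as the larger of the two calculations, as steps 2 and 3 show.

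**Step 2: post-intervention scores.**
- ARAT versus blank: Δ = 2.2; SD = √[(1.7² + 1.6²)/2] = 1.651; n = 12.9, so 13 per group.
- Non-specific versus blank: Δ = 0.2; SD = √[(1.9² + 1.6²)/2] = 1.756; 21.01 × (1.756/0.2)² ≈ 1,620 (1,622 by exact t). Power at 33 per group is about 7%.

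The larger of the two is about 1,620. A one-sided test still needs about 1,320. If rounding in Table 2 hid a true difference of 0.3, the figure would be about 721.

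**Step 3: change scores.** The difference in improvement is 1.8 for ARAT versus blank. For non-specific versus blank it is 0.4, in favour of blank.

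| Assumed r | ARAT vs blank: n | Power at 33 | Non-specific vs blank: n | Power at 33 |
|---|---|---|---|---|
| 0 | 44 | 80% | 859 | 10% |
| 0.5 | 23 | 98% | 430 | 14% |
| 0.8 | 11 | >99% | 174 | 29% |
| 0.9 | 7 | >99% | 88 | 50% |

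As an example, at r = 0 the non-specific SD of change is √(2.0² + 1.9²) = 2.759 and the blank SD is √(1.7² + 1.6²) = 2.335. The pooled SD is 2.555, and 21.01 × (2.555/0.4)² ≈ 858 (859 by exact t).

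ARAT versus blank gives 33 at r ≈ 0.26 (about 0.23 by the normal approximation). Non-specific versus blank gives 33 only at r of about 0.96 to 0.97, and then for a difference in the wrong direction.

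**Step 4: other routes.** Splitting α, inflating for a rank-sum test and using covariate-adjusted SDs were also tried. None makes 33 the larger of the two results. A three-arm F test needs about 14 to 29 per group, but that is not the calculation described.

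**Step 5: the contrast whose calculation is not described.** ARAT versus non-specific at 33 per group:
- Post scores: Δ = 2.0, SD 1.803, power about 99%.
- Change: Δ = 2.2, power 89% at r = 0 and 99% at r = 0.5.

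**Step 6: precision for non-specific versus blank at 33 per group.** The 95% half-width is t(0.975; 64 df) × SD × √(2/33).
- Post scores: 1.998 × 1.756 × 0.246 = 0.86 points.
- Change: 1.26 points at r = 0 (SD 2.555) and 0.89 at r = 0.5 (SD 1.808).

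**The case against.** The title calls the trial exploratory, the ARAT contrasts are well served on post scores, and no passage says that a non-significant non-specific versus blank result will be read as no effect. All of that is true. It limits the consequence, but it does not make the stated calculation right.

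The figure 33 may be a sound result that has been misdescribed. It fits ARAT versus blank on change at r near 0.26. ARAT versus non-specific on change at r = 0 comes close, at 33.3 by the normal approximation and 34.3 by exact t. Either origin is possible, but in both cases the paragraph misstates what was done, because it says that both comparisons with blank were calculated and the larger taken.

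The change-scale figures depend on a correlation the document does not give. This stands: at r = 0.9 the requirement falls to 88, so hundreds per group is not a lower bound. Only the post-score figure comes from Table 2 without an assumed correlation.

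A reader might also infer that ARAT versus non-specific acupoints was never sized, or that the trial is too small for it. The document supports neither. The article does not describe such a calculation, which is all a condensed account can show, and at the pilot effect 33 per group gives that contrast about 89 to 99% power.

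**Conclusion.** The point holds for one statement: 33 per group is not the maximum of the two calculations described, and the 90% power implied for non-specific versus blank is wrong. On post-intervention TNSS that contrast needs about 1,620 per group and has about 7% power at 33. On change, the scale the abstract names, it needs 859 down to 88 per group for r from 0 to 0.9, has 10 to 50% power, and points the other way in the pilot. These figures assume a two-sided test, Table 2 as printed and, for change, a common correlation in all arms.

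It does not follow that the trial should enrol about 1,620 per group, or that its ARAT comparisons are in doubt. At the pilot effects, power for ARAT versus blank is above 99.9% on post scores and 80 to 98% on change for r from 0 to 0.5. The lower end of that range is below the stated 90%, which is a further reason to state the scale and SD.

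**What to change.** Keep 111 participants and rewrite the Sample size paragraph:

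- State the contrast, the scale (post score or change), the SD and the sidedness that give 33.
- Withdraw the β = 0.1 claim for non-specific versus blank. Report that contrast as an estimate with a 95% confidence interval, and say that a non-significant result is not evidence of no effect. If an expected half-width at 33 per group is quoted, name its scale: about 0.86 points on post scores, or 1.26 to 0.89 on change for an assumed correlation of 0 to 0.5.
- State the power at 33 evaluable per group for ARAT versus blank (above 99.9% on post scores; 80 to 98% on change for correlation 0 to 0.5) and for ARAT versus non-specific (about 99% on post scores; 89 to 99% on change over the same range).
- If the pilot's individual data are at hand, replace the assumed correlation with the observed SD of change.

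The cost is protocol wording only, with no extra participants and no change to allocation. The downside is that one stated power figure becomes less favourable.
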